## Abstract

**Background:**

Mobile health, mHealth is recognized as a strategy to improve lifestyle behaviors. Research targeting specific lifestyle behaviors has shown that interventions using smartphones can be effective. However, few studies have evaluated solutions with multicomponent interventions, tailoring the intervention to the specific needs of the participant using a combination of mHealth and conventional treatment. To accomplish this, we developed Health Integrator, an mHealth platform with services and offers in the areas of diet, physical activity, sleeping habits, stress, alcohol and tobacco use. In the system, the user selects an area of intervention together with a health coach and set weekly goals. This study protocol presents the design and methodology of the Health Integrator Study, a randomized controlled trial to promote improved lifestyle behaviors.

**Methods:**

A three-arm parallel randomized controlled trial (1:1:1) is conducted in the Stockholm County, Sweden. In total, 209 employees at a four different companies representing both white and blue collar workers, have been recruited.

Participants are randomized to either a control group or to one of two intervention groups receiving a 3-month lifestyle behavior change program including either 1) use of Health Integrator and monthly health coaching sessions or 2) only Health Integrator.

At baseline and follow-up after 3- and 6-months, all participants answer questionnaires assessing lifestyle behaviors and quality of life. At baseline and the 3-month follow-up (end of intervention period), weight, height, waist circumference and blood pressure are measured, and all participants wear an Actigraph accelerometer for 7 days to assess physical activity. Blood lipid profile and HbA1c are measured among all participants at baseline. If baseline measures fall outside the normal range, a second measurement is done after 3 months.

**Discussion:**

The Health Integrator Intervention Study will evaluate if a personalized intervention combining mHealth and conventional programs for lifestyle change, with or without additional health coach sessions, can improve lifestyle behaviors and quality of life. Based on the results from this trial, Health Integrator can easily be implemented within a broad public.

**Trial registration:**

ClinicalTrials.gov Identifier: NCT03579342. Retrospectively registered, first submitted May 8, 2018.

## Background

Lifestyle is the single most important factor to improve health and decrease premature death [1]. There has been an exponential development of preventive initiatives using digital solutions for implementing lifestyle change, and tracking different types of health data such as exercise, diet, medications, stress and more. mHealth, defined by the World Health Organization, WHO, as “medical and public health practice supported by mobile devices, such as mobile phones, patient monitoring devices, personal digital assistants and other wireless devices” [2], has grown rapidly over the last couple of years. Previous mHealth studies have proven that it is possible to conduct lifestyle interventions using smartphones [3]. If the aim is better health at a lower cost, previous studies can be seen as proof-of-concept. Studies evaluating systems that are developed for dissemination in the population are crucial.

Since smartphones entered the market about a decade ago, they have become an important part of everyday life and can be used for tracking health and health related behaviors. In Sweden, 90% of the population own a smartphone and 98% have access to internet at home; ownership and usage is independent of socioeconomic status [4]. With this in mind, interventions using internet and smartphones may bridge the gap between individuals’ need for personalized health interventions and the regular health care’s lack of capacity to support these individuals. Additionally, the WHO Global Plan of Action on Workers’ Health clearly states that the health of workers must not only be protected, but also promoted in the workplace [5]. Intervening in work places may be a challenge due to different work tasks and schedules, but tailored lifestyle interventions using mHealth may be a solution.

Based on evidence from previous research, we have built a new digital platform for lifestyle change, called Health Integrator, to be used for example in work place settings. The platform is the product of a 5 day intense “design sprint” process, involving individuals from science, business, and innovation. It was further developed and prototyped through service design in collaboration with relevant stakeholders before it was launched to study participants in the described randomized controlled trial.

The Health Integrator platform offers a variety of public, private and community services for behavior change in different domains such as smoking, alcohol, physical activity, diet, stress, and sleep. This trial is a scientific evaluation of the efficacy of Health Integrator with an assortment of different lifestyle interventions to personalize health. The Health Integrator system is funded by the European Institute of Innovation and Technology, EIT, a European initiative to empower innovators to create innovative solutions for health as a part of Horizon 2020.

To scientifically evaluate the Health Integrator system, we are now conducting a randomized, controlled trial to determine the effectiveness of lifestyle intervention using mHealth.

### Aim

The aim of this paper is to describe the study design and methodology of the Health Integrator Intervention. We aim to evaluate if a digital platform accessible via a smartphone-app offering lifestyle intervention, with and without additional health coach guidance, can be used to make lifestyle changes and improve health related quality of life (primary outcome) in gainfully employed persons. Secondary outcomes include improving levels of blood pressure, body composition, blood lipids, HbA1c and other health related lifestyle factors.

### Hypothesis

We hypothesize that the subjects assigned to active intervention will have improved health related quality of life as well as improved cardiovascular risk factors after 3 months compared to the control group, and that improvements will last another 3 months after the intervention has ended. We further hypothesize that subjects in the intervention group receiving in-person support will achieve greater improvements than those with only digital support.

## Methods/design

### Study design

The Health Integrator intervention study is a three-arm parallel randomized controlled trial (1:1:1) conducted in the Stockholm County of Sweden. Assessments are done at baseline, and post intervention at follow-up after 3 and 6 months. See Fig. 1. The study protocol follows the SPIRIT 2013 Statement [6, 7] and the intervention is described according to the CONSORT EHEALTH checklist [8].

**Fig. 1 Fig1:**
[figure not shown]
Flow-chart of the Health Integrator study design

### Inclusion and exclusion criteria

Inclusion criteria are: age above 18 years, being able to read and understand Swedish well enough to understand the study aims and informed consent, having access to and being able to use a smartphone, and giving informed consent to participate in the study. Both men and women are eligible to participate. No specific exclusion criteria apply.

### Participants and recruitment

Four companies are participating in the Health Integrator Intervention study. Two companies with white-collar office employees, including personnel at an insurance company (Länsförsäkringar Alliance) and administrative personnel of Sweden’s largest pharmaceutical retailer (Apoteket AB). We also recruited blue collar employees, i.e. bus drivers, from two companies in Stockholm; at the largest bus transport group in the Nordic countries (Nobina) and at Europe’s largest transport provider (Arriva).

Study participants were recruited in two different ways according to the wishes of each company. The office of human relations at the two companies with white-collar employees sent an inquiry email about the study to their employees. Those who were interested in participating in the study responded to the first email and research personnel then received the email addresses. Bus drivers, whose email addresses are unknown to the employer, were continuously recruited by study personnel on site at the bus garages and asked in person to provide their private email addresses if they are interested in participation. Employees from all four companies that were interested in the study, were thereafter emailed information about the study and a link to access the web-based baseline questionnaire.

Eligible participants were required to give their informed consent for participation in the study in connection with the web-based questionnaire. After an introductory screen displaying information about the study, participants had to consent to participate in order to continue to the questionnaire. At completion of the questionnaire, the respondent was provided with a link to the Health Integrator system.

In the Health Integrator system, each user created an individual user account with personal log in details and responded to a health profile that included 38 questions on physical activity, diet, sleeping habits, stress, alcohol habits, and tobacco use (smoking and oral moist tobacco). The participant also scheduled a time for the baseline meeting with the health coach. The results from the health profile were not visible in the system at this point.

For participants receiving intervention, results from the health profile and the respondent’s status within each behavior were unlocked at the baseline meeting with the health coach and displayed using a colored scale and numbers to indicate if habits were good or could be improved. Green indicated that the reported health habit was very good, yellow that the reported health habit was good, orange that it needed to be improved and red that the reported health habit was associated with health risks and should be improved. See Fig. 2. Results for participants in the control group are unlocked at the follow-up meeting after 3 months.

**Fig. 2 Fig2:**
[figure not shown]
Screen shot from the Health Integrator. To the left, the color green indicates that the reported health habit is very good. In the middle, the color yellow indicates that it is good, while orange and red, found to the right, indicate that the health habit is unhealthy, can be improved, and should be targeted in the intervention

Written informed consent was additionally obtained at baseline assessments. All study participants meet with study personnel twice: at baseline and at the 3-month follow-up when body composition and blood pressure is assessed, participants respond to the lifestyle questionnaire, and they get a referral for laboratory tests. All participants are also given an accelerometer to measure physical activity during 1 week.

### Randomization and blinding

Once the participant had responded to the baseline questionnaire and scheduled a baseline meeting, they were randomized to one of the three arms using a random allocation list generated with STATA Version 14.0. We randomized by company and in blocks of 6 by gender.

The participant was randomized to 1 of 3 groups: 1) intervention using Health Integrator and a monthly telephone session with the health coach during the 3 months of follow-up (in total two sessions per participant) or 2) intervention using Health Integrator without extra health coach sessions or 3) control group which is not given any lifestyle advise during the intervention period. Subjects in the control group receive access to Health Integrator after 3 months when the active intervention is finished.

Due to the nature of the study, participants are informed about their allocation by study personnel at baseline assessments.

### Intervention

#### Overall

Participants in any of the two intervention groups receive a personalized intervention based on their health profile and tailored to the need of each specific participant. The aim for the individual participant during the intervention is to improve the chosen area of intervention which may be within domains of diet, physical activity, sleeping habits, stress, alcohol, tobacco use or other.

Adverse events or other unintended effects of the trial are voluntarily reported to the health coaches and will be reported.

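### The harms route described is voluntary report to health coaches, whose scheduled contact differs by arm, so recorded adverse events would not be comparable between arms

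*Protocol article*

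**What the plan says.** The harms method is stated in the protocol article under Intervention, Overall: "Adverse events or other unintended effects of the trial are voluntarily reported to the health coaches and will be reported". This fixes the mode (voluntary), the recipient (the health coaches) and the intention to report.

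Scheduled coach contact is set out under Randomization and blinding. The coach arm receives "a monthly telephone session with the health coach during the 3 months of follow-up (in total two sessions per participant"). The second arm is "intervention using Health Integrator without extra health coach sessions". The third is a "control group which is not given any lifestyle advise during the intervention period", and no coach session is described for it in that time.

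Some contact is common to all arms. Under Participants and recruitment, each person books a baseline meeting before randomization: "The participant also scheduled a time for the baseline meeting with the health coach". The same section says: "All study participants meet with study personnel twice: at baseline and at the 3-month follow-up". The Abstract adds: "At baseline and follow-up after 3- and 6-months, all participants answer questionnaires assessing lifestyle behaviors and quality of life". The instruments listed under Questionnaires include no item on injuries or unwanted effects.

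**The concern.** When events are recorded only if someone volunteers them, the number recorded depends on how often people have an occasion to speak to the recipient. Here the recipient is the coach, and coach contact is what distinguishes the first two arms. Two arms with the same true harms could show different counts simply because one was telephoned twice.

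The contrast between coach support and app alone is a declared interest of the trial (Hypothesis; Discussion). On the benefit side, every arm answers the same questionnaires. On the harms side, the opportunity to report is unequal. The offers include running and workout apps and gym passes (Intervention, Downloading), so exercise injuries are plausible. An app-only arm that looks safer only because nobody called would be misleading for a platform that the authors want to implement widely.

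**Working it through.** The documents state no harms rate, reporting probability or harms analysis, so there is no figure of the plan to reproduce. The sample-size calculation does not enter.

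**Step 1. Count scheduled contacts after baseline, up to month 3.**

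| Arm | Coach calls | 3-month meeting | Total if the meeting counts | Total if it does not |
|---|---|---|---|---|
| App + coach | 2 | 1 | 3 | 2 |
| App only | 0 | 1 | 1 | 0 |
| Control | 0 | 1 | 1 | 0 |

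The last two columns differ because the article says that study personnel hold the 3-month meeting. It does not say that a coach is present or that events mentioned there are recorded. The main calculation takes the milder case, in which the meeting counts.

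**Step 2. Model (assumed).** True harms are equal in all arms. Each event has the same chance q of being volunteered at each later contact, independently between contacts. With k contacts still to come, the chance that an event is recorded is 1 − (1 − q)^k.

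- App-only and control arms: k = 1, so the chance is q.
- Coach arm, all events before the first call: k = 3, so the chance is 1 − (1 − q)³.
- Coach arm, events spread evenly (one third before call 1, one third between the calls, one third after call 2): {[1 − (1 − q)³] + [1 − (1 − q)²] + q} / 3.

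**Step 3. Put the numbers in.** For q = 0.3 with even spread: (0.657 + 0.510 + 0.300) / 3 = 0.489, and 0.489 / 0.3 = 1.63.

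| q | Other arms | Coach arm, even spread | Ratio | Coach arm, all early | Ratio |
|---|---|---|---|---|---|
| 0.1 | 0.100 | 0.187 | 1.87 | 0.271 | 2.71 |
| 0.3 | 0.300 | 0.489 | 1.63 | 0.657 | 2.19 |
| 0.5 | 0.500 | 0.708 | 1.42 | 0.875 | 1.75 |
| 0.9 | 0.900 | 0.963 | 1.07 | 0.999 | 1.11 |
| 1.0 | 1.000 | 1.000 | 1.00 | 1.000 | 1.00 |

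**Step 4. Scale to this trial.** 209 / 3 is about 70 per arm. If 20% truly had an event (assumed), that is 14 per arm. With even spread, the expected recorded counts (coach arm against each other arm) are 2.6 v 1.4, 6.8 v 4.2 and 9.9 v 7.0 at q = 0.1, 0.3 and 0.5.

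**Step 5. The other contact count.** If the 3-month meeting is not a reporting occasion, the coach arm with even spread captures {[1 − (1 − q)²] + q + 0} / 3. This is 0.097, 0.270 and 0.417 at q = 0.1, 0.3 and 0.5. The other arms capture nothing through scheduled contact, so no ratio can be formed.

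**The case against.** A reader might infer that harms will be over-counted in the coach arm. The model does not support that: no arm records more than its true number of events. The coach arm is merely less incomplete, and the shortfall is larger in the other two. Nor is the difference certain. If nearly every event is recalled and recorded at a 3-month meeting that all arms attend, it all but vanishes.

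A reader might also infer that no other route exists. The article does not say so. It is a condensed account, and the full protocol may hold a harms form. Unscheduled reports are not excluded either, and the app-only arm does work with a coach at baseline to choose an area and set goals. What can be said is that no other route is described. Even so, the method that the article does state can be judged as stated; this is not a complaint about missing detail.

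The strongest objection is that no between-arm harms comparison is planned. The Aim, Hypothesis and Statistical analyses sections name no harms outcome or test, and a plain list of events would satisfy the text. This stands, and it limits the point to how any counts by arm can be read. It does not remove the point, because results are to be presented by group and readers of a three-arm trial will set harms side by side.

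Finally, the absence of meetings between months 3 and 6 might seem to add to the problem. It applies equally to all arms, so it creates no difference in capture.

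**Conclusion.** The concern holds as a likely difference in how completely harms are captured: fuller in the coach arm, poorer in the app-only and control arms. Both premises are in the text, namely voluntary report to coaches and two calls that only one arm receives. With the 3-month meeting counted as a reporting occasion and q between 0.1 and 0.5, equal true rates would appear 1.4 to 1.9 times as high in the coach arm if events are evenly spread, and 1.75 to 2.7 times as high if all occur early.

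These figures rest wholly on an assumed q that is constant and independent across contacts. Participants know their allocation, which could also change their willingness to report; the model leaves that out. The primary and secondary outcomes, the sample size and the planned efficacy analyses are unaffected. The change is worth making because it is cheap, but the trial's main conclusion does not depend on it.

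**What to change.** Add one identical question on injuries and other unwanted effects to the 3-month and 6-month questionnaires that all arms already answer. Base any by-arm harms table on those answers for the period from baseline to month 3.

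At month 6, ask about two periods separately: months 0–3, for those whose 3-month questionnaire came before the new item, and months 3–6. Controls gain access to the platform after month 3, so one undivided question would mix their control period with their time on the app. List events volunteered to coaches separately and descriptively, with a statement that coach contact differed by arm.

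The cost is one questionnaire item and a small amendment. Participants already past month 3 would have a longer recall period. Randomization is in blocks of 6, so they should be spread fairly evenly over the arms, but the table should show how many answered late. The item equalises the occasion to report; it cannot remove differences in reporting that arise because participants know their allocation.

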#### Downloading

The Health Integrator smartphone-application is compatible with both Android (version 4.1 and higher) and iOS (version 8 and higher).

For participants in one of the two intervention groups, each individual’s personal user account in Health Integrator was activated by the health coach at the baseline meeting. Based on the results from the health profile, the participant was helped to navigate to an area mutually chosen by the participant and health coach to be the intervention area of interest.

If, for example, the goal is to increase physical activity, a number of different offers are available to choose from in the Health Integrator system. This could for example be a smartphone-application like Runkeeper or the 7-min-workout, but also conventional training possibilities like a 3-month-training pass at the local gym, or a wrist support band to facilitate rehabilitation. The offers are all free of charge to the participant and quality checked by the health coaches before entered into the Health Integrator system. The participant and the coach have the possibility to choose among 37 offers in total in this version of the system.

#### Goal-setting

The health coach will help participants in the intervention groups to set achievable goals. Once a week the participant records if the weekly goal is met through a goal setting function in the Health Integrator system. This is done with smileys or by checking number of days the goal was met. A reminder is sent out every Sunday at 9.20 pm, prompting the participant to record to what degree the weekly goal was met.

### Study assessments

#### Biomarkers

At the baseline meeting, the participant got a referral to the nearest laboratory for venous blood sample taking. Baseline tests include hemoglobin A1c (HbA1c) in mmol/mol, total cholesterol (mmol/L), Apolipoprotein A1 (g/L) and Apolipoprotein B (g/L). If they are not within normal range at baseline, another measurement is conducted at follow-up, after 3 months, as would be done in clinical practice.

HbA1c is measured using the IFCC (International Federation for Clinical Chemistry and Laboratory Medicine) reference measurement procedure [9], Apolipoprotein A1 and B is analyzed with immunochemistry (turbidimetry) and cholesterol is analyzed with the enzymatic method using photometric reading [10].

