### Statistical analyses

Descriptive statistics will be produced to describe participant characteristics at baseline and follow-up. Results will be presented by control and intervention groups. Baseline characteristics will be produced to assess the success of the randomization in balancing characteristics. Differences between groups will be assessed using Student’s t-test and chi-square test for continuous and categorical variables, respectively.

Longitudinal data will be analyzed using both generalized estimating equations (GEE) and Mixed Models with a robust covariance structure to assess the effect of both time and the intervention itself on the study outcomes. Any unbalanced baseline characteristics will be controlled for in models. Interactions will be tested for in the models and intention to treat analysis will be performed to account for effects of cross-over and drop-out. Sensitivity analysis to account for missing data will also be done and to further study if the effect of the intervention differs based on participant characteristics.

Finally, we will also analyze how the app is perceived and used. At 3-month follow-up, the intervention group will receive a 16-item questionnaire evaluating the usability and satisfaction with the Health Integrator application. From the Health Integrator system, we will also be able to get descriptive statistics on number of log-ins, fulfilled goals per participant and which lifestyle interventions or services that were the most chosen ones among the participants in the intervention groups.

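### Lipids and HbA1c are unrestricted secondary outcomes but are re-measured only in participants abnormal at baseline, so the planned longitudinal models give a misleading time effect and an all-participant effect that rests on extrapolation

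*Protocol article*

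**What the plan says.** All references are to the protocol article.

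- **Outcomes (Aim).** "Secondary outcomes include improving levels of blood pressure, body composition, blood lipids, HbA1c and other health related lifestyle factors". No subset is named.
- **Hypothesis.** Active intervention is expected to bring "improved cardiovascular risk factors after 3 months compared to the control group". Again no subset is named.
- **Baseline sampling (Abstract, Methods).** "Blood lipid profile and HbA1c are measured among all participants at baseline".
- **Follow-up sampling.** The Abstract states: "If baseline measures fall outside the normal range, a second measurement is done after 3 months". The Biomarkers section gives the same rule, "If they are not within normal range at baseline, another measurement is conducted at follow-up, after 3 months", and explains it as following clinical practice. The panel is HbA1c, total cholesterol, apolipoprotein A1 and apolipoprotein B.
- **Analysis (Statistical analyses).** Longitudinal data go to both GEE and mixed models "to assess the effect of both time and the intervention itself on the study outcomes", with an intention-to-treat analysis and a sensitivity analysis for missing data. Nothing separates the selectively repeated markers from outcomes measured in everyone.
- **A looser statement.** The paragraph after the Fig. 2 caption (Participants and recruitment) describes the two visits, at baseline and 3 months, and says that "participants respond to the lifestyle questionnaire, and they get a referral for laboratory tests". This can be read as a referral for everyone at both visits.
- **Order of events.** Under Randomization and blinding, randomisation precedes the baseline meeting and allocation is disclosed at baseline assessments. Under Biomarkers, the blood referral is handed out at that same meeting.

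**The concern.** The outcome is stated for the whole trial but observed at follow-up only in people chosen because their first value was out of range. This is missingness by design, with zero chance of a planned follow-up value for participants in the normal range.

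Three consequences follow if the text is applied as written:

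1. In GEE on all available data, the month-0 mean describes everyone and the month-3 mean describes only the abnormal. The time effect then mixes change with a change of population. Weighting cannot repair this where the probability of re-measurement is zero.
2. A mixed model can use the observed baseline value, but what it says about normal-range participants comes from extending a fitted line into a region with no follow-up data.
3. Change among the re-measured includes regression to the mean, towards the normal range from whichever side the marker was abnormal.

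At stake is a claim that lipids or HbA1c improved over time, or improved across the whole study population, which the data could not support.

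**Working it through.** **The plan's own figure.** The only sample size given is 63 per group for the RAND-36 general health score: n = 2 × (1.960 + 0.842)² × (16/8)² = 62.8, so 63. It reproduces, but the point does not depend on it. The documents give no power, abnormal share or correlation for lipids or HbA1c.

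**Inputs from the documents.** 209 recruited, 1:1:1, so 209/3 = 69.7 per arm; two-sided 5%; 80% power.

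**Assumptions, not in the documents.** Marker standardised to mean 0 and SD 1, bivariate normal; correlation r = 0.8 between baseline and month 3; abnormality on the high side; share abnormal q of 10%, 20% or 30%; no drop-out.

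**Formulas.** Cut-off c = Φ⁻¹(1 − q).
- Mean baseline of the selected: m = φ(c)/q.
- Expected fall with no intervention: (1 − r)·m = 0.2m.
- Apparent rise if everyone's baseline mean is compared with the re-measured month-3 mean: r·m = 0.8m. This is the time effect from GEE with an independence working correlation.
- Detectable between-arm difference after baseline adjustment: (t₀.₉₇₅ + t₀.₈₀) × √(1 − r²) × √(2/n), with n = 69.7q, 2n − 2 degrees of freedom and √(1 − 0.64) = 0.6.

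| q | n per arm | m | Fall, no effect | Apparent rise, all vs re-measured | Detectable difference |
|---|---|---|---|---|---|
| 10% | 7.0 | 1.755 | 0.35 | 1.40 | 3.053 × 0.6 × 0.536 = 0.98 |
| 20% | 13.9 | 1.400 | 0.28 | 1.12 | 2.912 × 0.6 × 0.379 = 0.66 |
| 30% | 20.9 | 1.159 | 0.23 | 0.93 | 2.872 × 0.6 × 0.309 = 0.53 |

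All effects are in population SD. With follow-up on all 69.7 per arm, the same formula gives 2.822 × 0.6 × 0.169 = 0.29.

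**Wider range.** With q from 10% to 50% and r from 0.6 to 0.9, the fall with no effect runs from 0.08 to 0.70 SD. The adjusted detectable difference (normal approximation) runs from 0.29 to 1.20 SD in the subset, against 0.21 to 0.38 SD with follow-up on everyone.

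**Simulation of two arms (q = 30%, r = 0.75).**
- No effect: the re-measured fall 0.29 SD in both arms, the comparison of everyone's baseline with re-measured follow-up shows +0.87 SD, and the between-arm difference is about 0.
- Effect of −0.30 SD in abnormal participants only: the true all-participant effect is −0.09 SD. A linear missing-at-random model, fitted to the re-measured and extended to everyone, gives −0.30 SD.
- Constant effect of −0.30 SD: that model gives −0.30 SD, which is correct.

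So the extrapolated all-participant estimate is right only if the effect does not depend on the baseline value, and these data cannot test that in normal-range participants.

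**The case against.** The best defence is that the faulty analysis is inferred. The article refers generically to study outcomes, frames its hypothesis against control, and openly presents the repeat rule as clinical practice. A separate analysis plan might restrict these markers to the re-measured. That is fair as far as it goes, and no within-arm pre-post test is named. But the outcomes and hypothesis are stated without restriction, and the models are said to estimate a time effect with no exception. The mismatch is in the text.

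Four stronger readings are tempting and are not supported:

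- **That regression to the mean creates a false treatment effect.** It acts alike in randomised arms. The between-arm contrast among those abnormal at baseline is not biased by it, as the simulation shows.
- **That an all-participant effect cannot be estimated.** Missingness depends on the observed baseline value, so a mixed model can estimate it, at the price of extrapolation.
- **That the subset could detect only differences of about 1.6, 1.1 or 0.9 SD.** Those values come from using an SD of 1. They ignore the correlation of 0.8 and the baseline adjustment, which multiply them by 0.6.
- **That every marker will appear to fall.** The normal ranges are not given, and a marker abnormal because it is low would rise.

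Two points in the text remain open. The visit description can be read as a laboratory referral for all at 3 months. The Biomarkers wording also does not settle whether one abnormal value repeats that marker or the whole panel; under the latter, some normal-range values would be repeated.

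**Conclusion.** The point holds as a mismatch between how these outcomes are stated, how they are collected and how they are to be analysed. Applied as written, the plan yields a misleading GEE time effect and an all-participant intervention effect that depends on extrapolation.

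A usable comparison remains, between arms at 3 months among participants abnormal at baseline, but in a subset much smaller than the trial. One caution applies to it: the baseline sample is drawn after allocation is disclosed, so who attends, and hence who enters the subset, could differ by arm.

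The direction of the argument follows from the documents. The sizes do not: they rest on an assumed abnormal share, correlation, high-side abnormality and full retention. The primary outcome is unaffected.

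**What to change.** - Restate the lipid and HbA1c outcomes as the between-arm difference at 3 months among participants outside the normal range for that marker at baseline, adjusted for the baseline value.
- Leave these markers out of the all-participant GEE and mixed models.
- Do not interpret within-arm change or a time effect in these markers as an effect of the intervention.
- Report completion of both blood draws by arm.
- Reconcile the visit description after Fig. 2 with the repeat rule in the Abstract and Biomarkers section, and state whether an abnormal value leads to repetition of that marker or of the panel.

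The cost is wording only; the restatement itself calls for no extra blood tests. The downside is that conclusions on lipids and HbA1c narrow to a small subset.
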